#### Measures

##### PCT

The PCT Quiz assesses relevant knowledge about the relationship between cannabis and psychosis. It takes about 10 minutes to complete and involves 10 multiple-choice questions worth 1-point each, with scores ranging from 0 to 10. The researchers will read the questions aloud to reduce the impact of reading literacy. The details are described elsewhere regarding the development of the quiz, and its reliability and validity [42].

##### Postgameplay Survey

This survey explores the satisfaction with the gameplay experience. It was adapted from a randomized control study of video games designed to increase knowledge about antenatal care [62]. The items include “comfort with gameplay,” as well as enjoyment of the game, graphics, music, and story. Each item is rated as “Yes” (1 point) or “No” (0 points). Additional questions include the frequency of video gameplay and the types of devices used to play video games. The survey has been piloted with the Back to Reality Series involving Black youth [42].

#### Data Collection

##### Gameplay, Quantitative Test, and Qualitative Inquiry

This section will take 60-120 minutes. Each participant will be provided with a link to download the set of video games. A software program will randomly assign the order in which each participant plays the first game, the Back to Reality Series, or the control game on a 1:1 basis. It takes 45 minutes in total to play all the video games. Subsequently, the research staff will conduct the PCT Quiz by displaying the questions to the participants and reading out each item. Finally, the participants will play whichever game they had not played first.

##### Qualitative Interview

After a short break, the research staff will conduct qualitative interviews about the gameplay experiences and the perceptions of the mental health effects of cannabis and psychosis after playing the game. The participants will share how the perceptions of their own personal experiences with psychosis and cannabis might be influenced by their gameplay experiences. Participants will be asked about their views on the main character’s use of cannabis and their opinions about using video games for youth from Black communities.

#### Analyses

##### Qualitative Analysis

The same qualitative analysis and sample size procedures as outlined in Visit 2: Perspectives on Cannabis and Psychosis will be adopted for this analysis. However, the data sets from *Perspectives on Cannabis and Psychosis* and *Insight and Knowledge Acquisition* will be integrated during the analysis to detect changes in perception comparing pregame and postgame data sets to identify changes in insight or opinions. Triangulation of the feedback from different disaggregated racialized and gender groups will be performed to compare and contrast the views on cannabis and psychosis in order to identify relevant themes and ideas [63].

##### Quantitative Analysis

We will compare the performance of the groups on the PCT Quiz using the *t* test. A minimum difference of 18% in PCT Quiz scores represents a statistically and meaningfully significant increase in knowledge, based on a pilot study [45].

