### Visit 1: Baseline Assessments

#### Study Population

The eligibility criteria are as follows: (1) meet the criteria for a first episode of psychosis defined as the first illness episode involving psychosis symptoms; (2) meet DSM-5 (Diagnostic and Statistical Manual of Mental Disorders, 5th Edition) criteria for a psychotic disorder and a lifetime or current cannabis use disorder (up to 45% of people with a first episode of psychosis will meet the criteria for cannabis use disorder [16,47,48]; patients diagnosed with cannabis-induced psychosis by definition meet the criteria for both conditions [49] and will be eligible); (3) be between the ages of 16 and 30 years; (4) self-identify as a Black African or Black Caribbean first- or second-generation immigrant (English speaking), or belong to any ethnic group; (5) be a client of an early psychosis intervention with up to 12 months of service; and (6) be fluent in English.

Participants will self-identify and be divided into the following disaggregated ethnic and racialized groups: Black African (n=24), Black Caribbean (n=24), and any ethnicity (n=24). There may be significant differences in social and community norms for cannabis use between Black African and Caribbean groups and differences in English proficiency, educational attainment, and immigrant status. Sex will be defined based on sex assignment at birth. Gender will be self-assigned as man, woman, transgender, fluid, two-spirit, and non-binary. Equal numbers of men (including transmen) and women (including transwomen) will be enrolled for each racialized group. Participants will self-identify as nonimmigrant, or first- or second-generation immigrant.

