#### Assessment

Demographic data will be collected on gender, sex, age, ethnicity, education, living circumstances, language, income, immigrant status (first or second generation), employment, disability status, and DSM-5 diagnoses.

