#### Data Collection and Procedures

The video games will be streamed over Zoom by the research staff. Participants will be randomized to determine the gameplay order (either the Back to Reality Series or the control game will be played first). A software program embedded within the download of the Back to Reality Series randomly assigns the order in which each participant plays the first game on a 1:1 basis. The randomization is not to allocate participants into groups. The experimental and control games are packaged on the screen to protect the blinding at the outset. However, the video games are not associated with preconceived notions of therapeutic benefit, which minimizes bias. The video games are password protected, so participants will not have had prior access.

Subsequently, participants will complete a quiz measuring factual knowledge about the impact of cannabis on psychosis. Participants are randomized so that differences in quiz scores can be attributed to gameplay interventions, which is an advantage over pre-post gameplay designs for quantitative analysis. This process also avoids having participants complete the same or similar quiz twice in a day. The research staff will conduct the knowledge test by displaying the questions to the participants and reading out each item. After completing the quiz, participants will immediately play whichever game remains. Thus, if the participant was randomized to play the Back to Reality Series first, the control game, Morpheus’ Spell, will subsequently be played.** **Each participant will complete a gameplay survey about the Back to Reality Series. Finally, participants will undergo a second qualitative interview to discuss ideas and impressions from their gameplay experiences and reflect upon their views about the relationship between cannabis and psychosis after playing the game.

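### The quiz comparison uses an unadjusted t test; adjusting for predictors already recorded at Visit 1 would be a cheap but conditional gain in precision

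*Protocol article*

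**What the plan says.** Four parts of the protocol article bear on this.

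- **Analysis** (Visit 3, Quantitative Analysis): "We will compare the performance of the groups on the PCT Quiz using the" *t* test. No covariates are named. Regression is mentioned only among the analyses of the Visit 1 data.
- **Randomisation** (Visit 3, Data Collection and Procedures): embedded software "randomly assigns the order in which each participant plays the first game on a 1:1 basis".
- **No pre-game score** (same section): there is one quiz, after the first game, and the stated reason is: "This process also avoids having participants complete the same or similar quiz twice in a day".
- **What is known at Visit 1**: the Assessment section says "Demographic data will be collected on gender, sex, age, ethnicity, education", among other items. The Study Population section sets three groups of 24 (Black African, Black Caribbean, any ethnicity) and adds: "Equal numbers of men (including transmen) and women (including transwomen) will be enrolled for each racialized group". It also says that the Black African and Black Caribbean groups may show "differences in English proficiency, educational attainment, and immigrant status".

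**The concern.** The sample is deliberately mixed on racialized group and gender, and it will vary in education. If these factors predict quiz scores, an unadjusted t test leaves the variation they explain in the error term. The confidence interval is then wider than the same data could give. A baseline score is usually the best covariate, and here it is absent by design, so the Visit 1 variables are the main remaining source of precision. Chance imbalance between arms on these factors would also go uncorrected in the estimate. With 30 per arm and a factor split 50/50, the between-arm difference in proportion has a standard deviation of √(2 × 0.25/30) = 0.13.

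What is at stake is efficiency in a small trial, not validity.

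**Working it through.** **Inputs.** From the Visit 3 Sample Size section: pilot mean 6.5, SD 1.3 (10 participants), difference 18% × 6.5 = 1.17, standardised effect 1.17/1.3 = 0.9, 20 per group, dropout 15%. From the section on the games: the randomised pilot in homeless youth, with SDs of 1.6 and 1.9. Significance level and power are not stated; I assume two-sided 0.05 and 80%.

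**1. Reproduce the plan's figure.** n per arm = 2 × (1.96 + 0.84)² / 0.9² = 19.4, so 20. This matches. Power at 20 per arm is 0.81 by the normal approximation and 0.79 by the exact noncentral t. The exact t is used below.

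**2. Size of the pooled comparison.** 3 × 24 = 72 at Visit 1; 72 × 0.85 = 61, or about 30 per arm.

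**3. A second SD.** From the homeless-youth pilot, √((1.6² + 1.9²)/2) = 1.76. That is a different population, so it serves only as a sensitivity value.

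**4. Cost of adjustment.** Take k = 4 covariate terms: racialized group 2, gender 1, education 1. The residual SD is SD × √(1 − R²). The error degrees of freedom fall to 2n − 2 − k. Expected chance imbalance multiplies the variance by 1 + k/(2n − k − 3):

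- 20 per arm: 1 + 4/33 = 1.121
- 30 per arm: 1 + 4/53 = 1.075

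The variance breaks even where (1 − R²) times this factor equals 1, that is at R² = k/(2n − 3): 4/37 = 0.11 at 20 per arm and 4/57 = 0.07 at 30 per arm.

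**5. Power to detect 1.17 points.** R² is not in the documents, so a range is assumed.

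| Setting | Unadjusted | R² 0.05 | R² 0.1 | R² 0.2 | R² 0.3 |
|---|---|---|---|---|---|
| 30 per arm, SD 1.3 | 0.93 | 0.92 | 0.94 | 0.96 | 0.98 |
| 30 per arm, SD 1.76 | 0.72 | 0.71 | 0.73 | 0.78 | 0.83 |
| 20 per arm, SD 1.3 | 0.79 | 0.76 | 0.79 | 0.83 | 0.88 |

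At 30 per arm with SD 1.3, the 95% CI half-width goes from 0.67 points to 0.66, 0.62 or 0.58 for R² of 0.1, 0.2 or 0.3.

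**6. Many-category coding.** With 7 covariate terms at 20 per arm and SD 1.3, power is 0.74 at R² 0.1 and 0.79 at R² 0.2, against 0.79 unadjusted. The gain is gone.

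**7. Within one racialized group.** 24 less dropout is about 20, or 10 per arm. Racialized group is then constant, which leaves gender and education (k = 2). Unadjusted power is 0.48; adjusted power is 0.47, 0.51 or 0.57 at R² 0.1, 0.2 or 0.3.

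**The case against.** The strongest reply is that nothing here is wrong. Under 1:1 randomisation the t test is unbiased and holds its type I error, and its standard error already allows for chance imbalance. That stands. A reader might infer from the missing adjustment that the result would be biased or invalid, and the documents do not support that.

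A reader might also infer that precision is certainly being lost. That does not follow either. No association between these covariates and the quiz is given. The Study Population section says only that the two Black groups may differ. Fluency in English is an eligibility criterion, and the questions are read aloud to limit the effect of literacy. The nearest support is that undergraduates scored 7.55 and homeless youth 6.8 after the same game, but these were separate studies.

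Power figures that treat the covariates as free (0.83, 0.87 and 0.91 at 20 per arm for R² 0.1, 0.2 and 0.3) overstate the benefit. Charged properly, the gain at R² 0.1 is nil, and below that there is a small loss.

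Finally, this is a condensed article, and a fuller plan may name covariates or a balanced randomisation. For that reason the lack of any described stratification is not held against it. The article does, however, commit to a specific test, and that choice can be commented on as stated.

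**Conclusion.** This is a cheap improvement, not an error. At about 30 per arm, adjustment adds roughly 1 to 5 points of power with SD 1.3, where power is already 0.93, and roughly 1 to 11 points with SD 1.76, where it starts at 0.72. These gains assume R² between 0.1 and 0.3, a two-sided 5% level and four covariate terms. The downside is about 1 point at 30 per arm, or 3 points at 20 per arm, if R² is only 0.05, and more if gender or education is coded in many categories.

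The benefit belongs to the pooled comparison. A reader might hope that adjustment would also secure the separate hypotheses for the Black African and Black Caribbean groups. With power at 0.47 to 0.57 after adjustment, it would not.

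**What to change.** For the pooled comparison, prespecify a linear model of PCT Quiz score on:

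- randomised first game;
- racialized group (three levels);
- gender, grouped as in the recruitment quota, with a stated rule for participants whose gender falls outside those two groupings;
- education, as one ordered term.

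Report the adjusted mean difference with its 95% CI, and keep the unadjusted t test as a sensitivity analysis. Fix the coding before any scores are examined by arm.

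The cost is a sentence or two of analysis text and about four degrees of freedom, plus the small loss of power noted above if the covariates turn out to predict little. No new data are needed. The Results section describes recruitment as under way with full analysis to follow, so as of the article the change could still be made in advance.

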**Figure 1 figure1:**
[figure not shown]
The Back to Reality Series character Harry.

[name] produced the games adopting serious game design methodology [27] with an integrated knowledge translation community involving Black youth, young people with lived experiences of cannabis and psychosis, family members, game designers, clinicians, and researchers [42]. Focus group feedback from family physicians revealed that the Back to Reality Series delivered content relevant for youth in their practice about mental health and addiction [43]. Family physicians recommended offering the games to youth while patients were waiting for their appointments.

There have been small demonstration projects to pilot the use of the Back to Reality Series. Ten participants between 17 to 30 years of age with a first episode of psychosis felt that Harry’s Journey realistically portrayed psychosis experiences, and they enjoyed playing it [44]. Fifty-five youth experiencing homelessness (16-19 years of age) were randomized to play the Back to Reality Series versus a control game. Participants playing the Back to Reality Series demonstrated a significant mean knowledge test score advantage (mean 6.8, SD 1.6) compared to those playing the control game (mean 5.5, SD 1.9; *P*=.02) [45]. In 2020, 10 undergraduate students created tutorial objectives and content inspired by the Back to Reality Series. Using the Back to Reality Series as the focus of dialogue, student-led tutorials were conducted involving 9 Black youth (16-19 years of age) as participants. The participants demonstrated significant increases in their knowledge about cannabis, mental health, and pathways to care after playing the Back to Reality Series and engaging in the tutorials [42]. Qualitative analysis of the feedback revealed that the content was meaningful to them (eg “I guess the fact that Harry lived in a realistic teenage lifestyle that like a lot of youth can relate to and that made it more meaningful cause it felt more relevant.”) [42].

The control game “Morpheus’ Spell” is inert. It is a spelling “pop culture” digital game with no mental health content. It failed to increase knowledge about mental health and addiction when undergraduate students were randomized to play the Back to Reality Series first, obtaining a Psychosis and Cannabis Test (PCT) Quiz score of 7.55 (SD 1.04) versus a score of 7.82 (SD 0.40; *P*=.28) after playing the Back to Reality Series followed by Morpheus’ Spell [46].

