#### Hypothesis

We hypothesize a significantly greater knowledge test score (>18%) in the group first exposed to the Back to Reality Series compared to the control game. We expect this finding for Black African and Black Caribbean groups, Black men, Black women, and all ethnic groups with a first episode of psychosis and cannabis use disorder.

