#### Sample Size

Based on pilot data involving 10 participants with a first episode of psychosis, the mean baseline score was 6.5 (SD 1.3). The effect size is 1.17 (18% × 6.5) to detect a difference of 18%. The standardized effect size (E/S) is 0.9 (1.17/1.3 [effect size/SD]). The power calculations [64] suggest that 20 participants are sufficient per group. With a minimum of 24 participants per gender and racialized group at visit 1, there would be at least 20 participants per group by visit 3 (up to 4 weeks later), with a projected dropout rate of 15%.

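### A fixed 18% difference in quiz score is presented as marking statistical significance, which it cannot do at the trial's own sample sizes

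*Protocol article*

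**What the plan says.** Four places in the protocol article bear on this.

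- **Visit 3, Quantitative Analysis.** The groups are compared on the PCT Quiz with a t test. The section then adds: "A minimum difference of 18% in PCT Quiz scores represents a statistically and meaningfully significant increase in knowledge, based on a pilot study". The pilot it cites is the randomized one in youth experiencing homelessness.
- **Visit 3, Hypothesis.** The statement is: "We hypothesize a significantly greater knowledge test score (>18%) in the group first exposed to the Back to Reality Series compared to the control game". The result is expected in the Black African and Black Caribbean groups, in Black men and Black women, and across all ethnic groups.
- **Visit 3, Sample Size.** A different pilot, in 10 people with a first episode of psychosis, supplies a mean of 6.5 and an SD of 1.3. The 18% becomes 1.17 points and a standardized effect of 0.9, and "The power calculations [64] suggest that 20 participants are sufficient per group".
- **The Back to Reality Series and the Control Game Morpheus' Spell.** The summary of the randomized pilot reports: "significant mean knowledge test score advantage (mean 6.8, SD 1.6) compared to those playing the control game (mean 5.5, SD 1.9"), in 55 participants, P=.02.

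**The concern.** The sentence in the analysis section joins two different ideas. Whether a difference is meaningful is a judgement about size, and can be fixed in advance. Whether it is statistically significant depends on how precisely it is estimated, and changes with every sample size at which the comparison is made. The hypothesis is to be examined both in the full sample and in groups about a third of that size, so no single percentage can serve as the significance mark in all of them.

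The quiz is the only quantitative measure of knowledge acquisition in the plan. If one analyst follows the t test and another follows the 18% sentence, they can reach opposite conclusions from the same data. The source of the 18% also matters, because the figure is credited to a pilot whose reported means do not give it.

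**Working it through.** **Inputs.** SD 1.3, mean 6.5 and a difference of 0.18 × 6.5 = 1.17 points (Sample Size); 1:1 randomization of play order (Data Collection and Procedures); 24 participants in each of three ethnic groups, 72 in all (Study Population); 15% dropout (Sample Size). The article does not give alpha, sidedness or power. I assume two-sided 5% and, for the sample size, 80% power.

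**1. The plan's own figure.** n per arm = 2 × (1.96 + 0.8416)² × (1.3/1.17)² = 2 × 7.849 × 1.235 = 19.4, so 20. The stated figure reproduces. The exact t calculation gives 21. Power at 20 per arm is 81.2% by the normal approximation and 79.2% by the exact t.

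**2. Arm sizes at Visit 3.** Full sample: 72 × 0.85 = 61, or about 30 per arm. One racialized group: 24 × 0.85 = 20.4, or about 10 per arm when split 1:1.

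**3. Smallest significant observed difference.** This is t(0.975, 2n − 2) × 1.3 × √(2/n).

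| Per arm | Smallest significant difference | As % of 6.5 |
|---|---|---|
| 30 (full sample) | 0.67 points | 10.3% |
| 20 (planning figure) | 0.83 points | 12.8% |
| 10 (one racialized group) | 1.22 points | 18.8% |

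In the full sample, differences of roughly 11% to 17% would be significant by the t test yet fall below the stated minimum. At 10 per arm, an observed 1.17 points gives t = 1.17/(1.3 × √(2/10)) = 2.01 on 18 df, p about 0.06. That would reach the 18% mark without being significant at 5%.

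**4. If 18% were a bar on the observed difference.** With a true difference of 1.17, the estimate is distributed symmetrically about 1.17, so the chance of observing at least 1.17 is 50% at any sample size. Simulation at 10 to 36 per arm gave 49.9% to 50.3%. For an 80% chance of clearing such a bar at 20 per arm, the true difference would have to be 1.17 + 0.8416 × 1.3 × √(2/20) = 1.52 points, or 23.3% of 6.5.

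**5. The cited pilot.** 6.8 − 5.5 = 1.3 points. That is 1.3/5.5 = 23.6% of the control mean, 1.3/6.8 = 19.1% of the intervention mean, 1.3/6.5 = 20.0% of the planning mean, and 1.3/10 = 13% of the scale. None of these is 18%.

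**The case against.** The strongest reply is that the only test named is the t test, and that 18% is simply the smallest difference of interest on which the trial was sized. That is ordinary practice. Any trial powered at its minimum important difference has an even chance that the estimate exceeds that value when it is the truth; this is symmetry and no defect. The reply stands as far as it goes. A reader might infer from the >18% in the hypothesis that success requires an observed difference above 18%, and so that the trial has only a 50% chance of success at its planning effect. The protocol does not expressly state such a rule, so the 50% is conditional on that reading.

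A reader might also infer that the 18% was wrongly attributed to the pilot. The documents do not support that either. A minimum meaningful difference may be set below a pilot's observed effect, the pilot report is not at hand, and its arm sizes are not given. If the 55 were split 27/28, the pilot's smallest significant difference would be about 0.95 points, or 17.3% of 5.5 (17-20% over the splits tried), so 18% might loosely be its significance boundary. That is conjecture, and a boundary for one trial's size and SD would not carry over to another. What can be said is that the derivation is not shown.

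Nor is the unit left open: the Sample Size section fixes it as 18% of 6.5. The subgroup miss is narrow (1.17 against 1.22 points), and reporting the t test's p value would reveal it.

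None of this rescues the claim that an 18% difference is in itself statistically significant.

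**Conclusion.** The sentence in the analysis section is wrong as written, and the >18% in the hypothesis leaves it unclear what decides the result. On the protocol's SD of 1.3 and an assumed two-sided 5% level, the significance boundary runs from about 10.3% in the full sample to 18.8% within one racialized group, so 18% is too strict a mark in the first and slightly too lenient in the second. These arm sizes assume the projected dropout and an even split by play order.

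The sample size arithmetic is unaffected: 20 per arm gives about 79-81% power for the t test at 1.17 points. The drop to 50% applies only if 18% is used as a bar on the observed difference. On the source, the finding is limited to this: 18% cannot be derived from the pilot figures shown. This is a misstated threshold that should be corrected, and it does not invalidate the design.

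**What to change.** - In the Hypothesis and Quantitative Analysis sections, state that significance is judged by the t test of a zero mean difference at a two-sided 5% level, and that the difference will be reported in quiz points with its 95% CI.
- Delete the word *statistically* from the 18% sentence, and remove >18% as a condition of success in the hypothesis.
- Keep 1.17 points (18% of 6.5, on the 0 to 10 scale) only as the planning difference and the benchmark for judging whether the estimate and its interval are meaningful.
- State how 18% was obtained, since the pilot as summarized shows 1.3 points (23.6% of the control mean).
- If the sponsor does intend to require an observed difference of at least 18%, say so and size the trial for that rule.

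The first four changes cost wording only; they alter neither the data collected, nor the randomization, nor the sample size. The last would require a new power calculation.
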